## Results

Recruitment for this study began in November 2014. As of June 2015, we met our enrollment goal of 80 patients. However, because of differences in site policies, the distribution of enrolled participants does not match our initial goals. By site, we have enrolled 40 participants from Bellevue Hospital Center, 31 from Gouverneur Health, and 9 from Woodhull Medical Center. As Woodhull Medical Center is located in a different part of New York City and serves a slightly different patient population, we plan to return to that site within the next few months to recruit an additional 11 patients.

Out of these 80 participants enrolled, the 71 from Bellevue Hospital Center and Gouverneur Health have been invited to attend the PEP intervention. Because of staff turnover and site-specific policies, we have as of yet been unable to hold any PEP intervention sessions at Woodhull Medical Center. Of the 71 participants invited to attend the PEP intervention, 45 have attended PEP session 1, 36 have attended the full PEP intervention, and 33 have returned for the post-PEP focus group. Of the 11 participants switched from the immediate intervention group to the deferred intervention group, 6 completed the T1 assessment and 3 attended at least one session of the PEP intervention. Coding and thematic analysis of the focus group discussions is not completed, but participants have reported that the PEP intervention was not only acceptable but a valuable experience that made them feel more empowered in their own health care. Several participants have even reported seeing their HCPs after completing the PEP intervention and changing their behaviors in the visit, which resulted in improvement in the quality of their visit.

Follow-up data collection is still underway and all patients who attended at least PEP session 1 will be called for all follow-up data points. Follow-up data collection is scheduled to conclude in April 2016 and the results of our data analysis are expected to be available by June 2016.

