## Methods

### Overview

The PEP is a randomized, wait-list control study (see
Multimedia Appendix 1) that aims to enhance general communication skills so that patients can participate in SDM during office visits, become activated in their own health care, and better manage their medical conditions.

Patients were recruited in cohorts of 20 and then randomly assigned to attend the PEP intervention immediately (immediate intervention) or after a waiting period (deferred intervention). All participants completed a baseline assessment at the time of enrollment (T0) and will complete follow-up assessments 1 week (T2), 3 months (T3), and 6 months (T4) after completion of the PEP intervention (see
Figure 1). Additionally, the deferred intervention group was assessed at the end of the waiting period (T1), immediately before being invited to attend the PEP intervention. The T1 assessment for the deferred intervention group was approximately 3-4 months after randomization and was timed to coincide with the T3 assessment of the immediate intervention group. A wait-list control design was chosen to create a control group with multiple time points of data collection (deferred intervention T0-T1) while still allowing for all participants who enrolled in the study to complete the PEP intervention and post-PEP follow-ups.

Aside from attending the PEP intervention, all participants continued to receive their usual care, including all scheduled primary care and specialty clinic appointments, HbA
_1c_monitoring, and all medications as directed by their physicians.

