### Follow-Up

After completion of the PEP intervention, participants will be followed up for 6 months and will complete repeat assessments at 1 week (T2), 3 months (T3), and 6 months (T4) after the PEP intervention (see
Table 1). The T2 assessment will take place either at the beginning of the focus group, to avoid any bias introduced by discussing the PEP intervention again, or by telephone for any participants who do not come to the focus group. The T3 and T4 follow-ups will occur by telephone and any concurrent HbA
_1c_available at these times will be collected from the EMR.

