### Sample Size

Prior studies have pilot-tested interventions to increase patient activation and found that PAM scores increased by a range of 4-8 points [
30,
31]. This difference was statistically significant, is thought to be clinically significant, and translates to a moderate effect size, Cohen’s
*d*=0.48. Given the repeated-measures design of the study, setting alpha = .05 and beta = .2, and using the effect size calculated from the literature, the required sample size will be n=36 patients. It is our goal to have 40 participants complete the PEP intervention.

In anticipation of significant participant dropout over the course of the study, we aimed to enroll 40 patients from Bellevue Hospital Center, 20 from Gouverneur Health, and 20 from Woodhull Medical Center. From these patients, it was our goal that 20 from Bellevue Hospital Center and 10 each from Gouverneur Health and Woodhull Medical Center would complete the PEP intervention. Because of these concerns about dropout, all participants who were randomized to the immediate intervention group but unable to attend the PEP intervention at that time were contacted for the T1 assessment with the deferred intervention group and invited back to attend the PEP intervention as part of that group (see
Figure 1).

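### The 3-month outcome in the immediate arm is measured on PEP attenders, while its matched control (deferred T1) is taken before attendance is known, so the only randomised comparison with untreated patients is open to selection

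*Protocol article*

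**What the plan says.** All places are in the protocol article.

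- **Purpose of the control (Overview).** "A wait-list control design was chosen to create a control group with multiple time points of data collection", namely the deferred arm between T0 and T1.
- **Control measurement (Overview).** "the deferred intervention group was assessed at the end of the waiting period (T1), immediately before being invited to attend the PEP intervention". This T1, about 3-4 months after randomisation, "was timed to coincide with the T3 assessment of the immediate intervention group".
- **Clock for T2-T4.** The Overview states: "All participants completed a baseline assessment at the time of enrollment (T0) and will complete follow-up assessments"; the same sentence then dates those assessments from completion of PEP. The Follow-Up section agrees: "After completion of the PEP intervention, participants will be followed up for 6 months".
- **Who is called (Results).** "all patients who attended at least PEP session 1 will be called for all follow-up data points".
- **Immediate-arm patients who do not attend (Sample Size).** Those "unable to attend the PEP intervention at that time were contacted for the T1 assessment with the deferred intervention group", and they were invited to PEP as part of that group. Results reports 11 such patients: 6 completed T1 and 3 attended at least one session.
- **Attendance, both arms together (Results).** "Of the 71 participants invited to attend the PEP intervention, 45 have attended PEP session 1, 36 have attended the full PEP intervention".
- **Analysis (Data Analysis).** The tests are within group, then pooled before and after PEP. The arms are set against each other on outcomes only through the group and time terms of the mixed models.

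**The concern.** Whether someone attends PEP is decided after randomisation and may well be related to activation, the primary outcome. People who come to group sessions might have gained on the Patient Activation Measure (PAM) without PEP, or gained more than those who stayed away.

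Immediate T3 against deferred T1 is the only point at which a randomised, untreated group is measured alongside a treated one. If one side of it holds attenders and the other holds everybody, a difference in trend between attenders and non-attenders is read as an effect of PEP. Moving non-attenders out of the immediate arm and assessing them with the controls would push in the same direction. Outcomes that were never collected cannot be restored at the analysis stage. A mixed model helps only if the missing values are missing at random given what was observed.

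**Working it through.** **1. The plan's own figure.** Sample Size gives n=36 from d=0.48, alpha .05 and beta .2 with repeated measures. As a two-sided paired test, ((1.960 + 0.842)/0.48)² = 34.07, so 35 by the normal approximation; with the noncentral t, power at 36 is 79.96%. The figure reproduces and is not in dispute. It rests on a before-after change, not on a difference between arms.

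**2. Who is measured at 3-4 months after randomisation.**

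| Randomised arm | Attends when first invited | Does not attend then |
|---|---|---|
| Immediate | T3, as immediate | No T3; those moved are contacted for T1 with the deferred group (6 of 11 completed it) |
| Deferred | T1 (not yet invited) | T1 (not yet invited) |

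The immediate cell that enters T3 is selected on attendance. The deferred cells are not. The three moved patients who attended later have T2-T4 dated from that later course, so their value at the common time point is still their T1.

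**3. Size of the shift with no true PEP effect.** Let *q* be the share of the immediate arm left out and *g* the difference in change, without PEP, between attenders and non-attenders (in SD). The attender mean exceeds the whole-arm mean by *q* × *g*.

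- *q*: the only arm-specific count is the 11 moved. The arm size is assumed: 40 from 1:1 allocation of 80, or 36 as about half of the 71 invited. So *q* = 11/40 = 0.275 or 11/36 = 0.306.
- *g*: 0.2 to 0.3 SD, an assumption; the article gives nothing on it.

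| *q* | *g* = 0.2 | *g* = 0.3 |
|---|---|---|
| 0.275 | 0.055 SD (11% of 0.48) | 0.083 SD (17%) |
| 0.306 | 0.061 SD (13%) | 0.092 SD (19%) |

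**4. If the 6 moved patients with T1 are also counted as controls.** Assume the same share of eventual non-attenders in the deferred arm and complete T1 there. The shift becomes the non-attender share of the enlarged control group times *g*.

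- 36 immediate, 35 deferred: (35 × 0.306 + 6)/(35 + 6) = 16.7/41 = 0.41, giving 0.08 to 0.12 SD (17-25% of 0.48).
- 40 and 40: (11 + 6)/(40 + 6) = 17/46 = 0.37, giving 0.07 to 0.11 SD (15-23%).

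**The case against.** Several counter-arguments have force.

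- **The plan names no direct T3-versus-T1 test.** This is true: the sample size and most tests concern change within people. But the wait-list arm is justified as a control group, T1 is timed to match T3, and group enters the mixed models. That this is the only randomised comparison makes it more worth protecting.
- **The Results rule does not say that only attenders are called.** This is also true. The reading rests on two facts together: T2-T4 run from completion of PEP, and no section schedules them for people who never attend.
- **Baseline differences between attenders and non-attenders will be tested.** That covers T0 values, not trend.

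A reader might also infer more than the article supports:

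- *That the Overview promises follow-up of everyone and Results contradicts it.* The Overview sentence already conditions follow-up on completing PEP. Results, if anything, widens it to people who attended only session 1.
- *That no as-randomised estimate is possible at 3 or 6 months.* At 3 months an incomplete one can be built, because 6 of the 11 moved patients have T1. At 6 months the untreated control is gone because the deferred arm has by then been offered PEP; the design causes that, not the calling rule.
- *That the loss is 26 of 71 (37%) or 35 of 80 (44%).* The first pools both arms and is an interim count while sessions continue. The second adds 9 Woodhull patients who had not yet been invited.
- *That T1 covers every deferred patient.* It targets them all, but no completion figure is given for that arm.
- *That the 45 − 36 = 9 people who had attended session 1 but not the full PEP fall outside follow-up.* They are to be called at all points, and some may still finish. Their anchor date is detail that an article may leave to the full protocol.

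**Conclusion.** The concern stands for the 3-4 month comparison between arms. Immediate T3 depends on attendance after randomisation and deferred T1 does not. The handling of the moved patients adds to the imbalance unless they are analysed in the arm to which they were randomised, which the article does not state.

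Neither the size nor the direction of the bias can be derived from the article. Under the stated assumptions (11 of 36-40 left out, a gap of 0.2-0.3 SD in favour of attenders) the shift is about 0.06-0.09 SD, or 11-19% of d=0.48. It is about 0.07-0.12 SD if the moved patients also sit among the controls. Non-attenders in the immediate arm beyond those 11 are not reported and would raise these figures. The stated n=36 is unaffected.

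**What to change.** 1. Assess every randomised participant at the common point 3-4 months after randomisation, whether or not they attended PEP. Where that window has closed, call as soon as possible and record the actual date. A deferred participant who has since had PEP can no longer supply an untreated value.
2. Use the moved patients' T1 as their 3-month outcome in the immediate arm.
3. State that immediate T3 against deferred T1, and the group term in the mixed models, are analysed by randomised arm.
4. Keep the T2-T4 schedule after PEP for attenders in both arms, and report the attender-only before-after analyses as secondary. Recounting T3 and T4 from randomisation for everyone would not serve: it would roughly duplicate the deferred T1 and lose that arm's planned assessment 6 months after PEP.

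The cost is a limited number of extra telephone questionnaires by the existing research assistants. It begins with the 11 − 6 = 5 moved patients without T1. Among the 71 invited, never-attenders cannot exceed the 26 in both arms who had not attended when Results was written, and those in the deferred arm are due T1 anyway. A few sentences must be added to the plan, and the estimated effect may be smaller. Follow-up was open until April 2016, so the change was still possible in part.

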## Discussion

Although there have been significant shifts in the power hierarchy between HCPs and patients, there continues to be an asymmetry that makes it difficult for patients to engage in true SDM as envisioned by the PCMH model. Little is understood about how to best activate patients to make the most of their visits with HCPs. With input from both patients and HCPs, we have developed an innovative PEP that seeks to prepare patients with T2DM to be better partners in their care and collaborate effectively with HCPs. We focused on improving patients’ communication skills in the context of the medical encounter by discussing behavioral descriptors for activated patients and then using performance-based training, adapted from SP methodology, to develop these skills.

Study enrollment and implementation of the PEP intervention have been shown to be feasible across multiple hospital sites and acceptable to patients. Participants were able to engage in the skills development tasks and to self-reflect on their experiences with HCPs. Initial qualitative responses from participants were positive and collection of quantitative post-PEP data will conclude over the next few months, which will allow us to assess the effect of this intervention on patient activation and self-reported measures of diabetes care.

## Appendix

Multimedia Appendix 1 CONSORT-EHEALTH checklist V1.6.2 [
62].

## Abbreviations

AURA: Ask, Understand, Remember Assessment
DSMQ: Diabetes Self-Management Questionnaire
EMR: electronic medical record
HbA1c: hemoglobin A1c
HCP: health care provider
Krantz: Krantz Health Opinion Survey
NVS: Newest Vital Sign
PAM: Patient Activation Measure
PCMH: patient-centered medical home
PCS: Preference Control Scale
PEP: Patient Empowerment Program
RA: research assistant
SDM: shared decision-making
SHP: standardized health care provider
SP: standardized patient
T2DM: type 2 diabetes mellitus
